### Assignment of interventions: blinding

#### Who will be blinded

Participants will be blinded to their group assignment (intervention or control). They will not know whether they are receiving active dual-target a-tDCS or sham stimulation, ensuring that their expectations do not influence the outcomes.

The therapists administering the tDCS will not be blinded to the group assignments. They will know whether they are providing active or sham stimulation due to the nature of the intervention.

Outcome assessments will be conducted by clinicians who are blinded to the participants’ group assignments. Each participant will be identified by a unique study number, and the outcome data will be recorded without revealing the group allocation.

Data analysis will be performed by an independent data analyst who will be blinded to the group assignments. The analyst will work with de-identified data, ensuring that the analysis remains unbiased.

#### Procedure for unblinding if needed

Unblinding will only be considered in specific circumstances where it is deemed essential for the participant’s safety, such as in the case of a serious adverse event that requires knowledge of the treatment received for appropriate medical intervention.

### Data collection and management

#### Plans for assessment and collection of outcomes

All assessors will undergo rigorous training in the administration of cognitive assessments and fNIRS measurements to ensure consistency and accuracy. Standardized operating procedures will be developed and followed for all data collection processes, including detailed instructions on administering each assessment tool. All data collection forms will be available upon request and will be stored securely within the study’s data management system.

#### Plans to promote participant retention and complete follow-up

To enhance participant adherence, a research assistant will send reminders via phone calls and text messages to ensure they attend all scheduled assessments and intervention. If participants discontinue or deviate from intervention protocols, the study team will initiate contact and prioritize addressing any concerns that may be impacting their adherence to the intervention protocols. Transportation reimbursements will be provided to encourage participants to complete the study.

#### Data management

All data collected during the trial, including baseline, intervention, and follow-up assessments, will be entered into a secure electronic database using the China Clinical Trial Registration Center’s electronic data management platform (ResMan Research Manager). Data entry will be performed by trained personnel following standardized protocols to ensure accuracy and consistency. To minimize data entry errors, a double data entry process will be employed, where two independent data entry personnel will input the data separately. Any discrepancies between the two entries will be resolved through a verification process by a third party. All participant data will be anonymized using unique participant identification codes, replacing personal identifiers to maintain confidentiality. Hard copies of any paper-based data collection forms will be stored in locked filing cabinets within a restricted access area at the study site to ensure data security.

#### Confidentiality

This trial will follow the Personal Information Protection Law of China. The database will be kept confidential and anonymous. Personal information about potential and enrolled participants will be collected only by authorized members of the research team. Only the minimum necessary information will be collected to achieve the trial’s objectives, which includes demographic data, medical history, contact details, and any other relevant information necessary for the conduct of the trial. All personal information will be stored securely. Personal identifiers, such as names and contact information, will be removed or replaced with unique participant codes in the main study database. No study details can be disclosed to unauthorized third par-ties without prior approval.

#### Plans for collection, laboratory evaluation and storage of biological specimens for genetic or molecular analysis in this trial/future use

Not applicable. No specimens will be collected.

### Statistical methods

#### Statistical methods for primary and secondary outcomes

The primary outcome of this study is the change in MoCA scores from baseline to post-intervention and follow-up. The changes in MoCA scores from baseline to post-tDCS intervention, and during the follow-up assessment, will be compared between the experimental and control groups. Homogeneity of variance will be assessed by Levene’s test. For normally distributed continuous data, ANOVA will be used to compare differences between the two groups. If ANOVA indicates significant differences, further post-hoc analysis will be performed using Bonferroni correction. For non-normally distributed continuous data, the Wilcoxon test will be used. The significance level (α) for statistical hypothesis testing will be set at *P* < 0.05. Differences with *P* < 0.05 will be considered statistically significant, while those with *P* > 0.05 will be considered not statistically significant.

Secondary outcomes, including changes in DST, TMT-A and TMT-B, and MBI scores, will be analyzed using similar repeated measures ANOVA methods. For non-normally distributed continuous data, the Wilcoxon signed-rank test will be used for within-group comparisons, and the Mann-Whitney U test will be used for between-group comparisons. fNIRS data will be analyzed using mixed-effects models to assess changes in cortical activation and connectivity, accounting for random effects of participants and fixed effects of group and time. Correlation analysis, such as Pearson correlation coefficient or Spearman correlation coefficient will be conducted to explore the relationships between primary and secondary outcome measures. Lesion location (cortical/subcortical), stroke subtype (ischemic/hemorrhagic), hemispheric lateralization (left/right) and stroke phase (subacute/chronic) will be recorded based on imaging reports. Exploratory analyses may include lesion location and laterality as covariates if appropriate, to explore their influence on intervention outcomes.

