### Outcomes

#### Primary outcomes

The MoCA is a cognitive screening tool that evaluates multiple domains, including memory, attention, language, and executive function. It has proven to be highly reliable and valid in stroke patients, with a test-retest reliability of 0.96 and inter-rater reliability of 0.87–0.95 in Chinese versions. The MoCA is more sensitive than the mini-mental state examination (MMSE) for detecting cognitive impairment in stroke patients (Zuo et al., 2024), making it an ideal choice for assessing post-stroke cognitive deficits.

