### Sample size

The primary outcome measure for this trial is the MoCA score after 10 treatment sessions. The sample size estimation was conducted using a two-sample means comparison. Based on similar published studies (Gonzalez et al., 2021), it is known that the mean MoCA scores after treatment in the experimental group and the control group are assumed to be 25.7 and 23.7, with standard deviations of 2.4 and 1.7, respectively. With a significance level of α = 0.05 (two-sided test) and a power of 1-β = 0.9, assuming equal sample sizes for the experimental and control groups, the following formula was used:

n=(Z1-α/2+Z1-β)2×(σ12+σ22)δ2

In the formula: Z_1−α/2_ = 1.96, Z_1−β_ = 1.28, σ_1_ and σ_2_ are the pooled standard deviation of the two groups, and δ is the difference between the two group means.

Using the “Two-Sample *T*-Tests Allowing Unequal Variance” option in PASS 2021 software, the calculation determined that each group requires 24 subjects. Considering a dropout rate of 20%, 30 subjects will be enrolled in both the experimental and control groups, totaling 60 subjects, to ensure the scientific rigor of the study design.

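### The primary outcome is stated inconsistently (MoCA at Week 2 only, or change at Week 2 and Week 14), and the plan does not fix which comparison decides success

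*Protocol article*

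**What the plan says.** Three places in the protocol article bear on the primary outcome.

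- **Sample size:** "The primary outcome measure for this trial is the MoCA score after 10 treatment sessions". The calculation uses group means and SDs of the score after treatment, so it covers one variable at one time. The Participant timeline places this assessment at the end of Week 2.
- **Statistical methods for primary and secondary outcomes:** this section instead states "The primary outcome of this study is the change in MoCA scores from baseline to post-intervention and follow-up". It then plans a comparison of the two groups on MoCA change at each of those assessments. This is a change score at two times, Week 2 and Week 14.
- **Primary outcomes:** "The MoCA is a cognitive screening tool that evaluates multiple domains, including memory, attention, language, and executive function". This section describes the instrument and its reliability, and gives neither a time point nor a metric.

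On error control, the Statistical methods section says "The significance level (α) for statistical hypothesis testing will be set at *P* < 0.05", without dividing alpha between times. It adds "If ANOVA indicates significant differences, further post-hoc analysis will be performed using Bonferroni correction". For non-normal data it names the Wilcoxon test and mentions no correction. Secondary outcomes "will be analyzed using similar repeated measures ANOVA methods", which suggests that MoCA is also meant to be analysed in a repeated-measures model.

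**The concern.** The primary outcome fixes what the trial's conclusion rests on, and here two sections answer that question differently. A result significant at Week 2 but not at Week 14, or the reverse, has no agreed reading. It could be called positive under one section and negative or undecided under the other, and the choice could be made after the data are seen. The Week-14 comparison was also never sized, because the Sample size section gives no effect or SD for it. A fuller document could add detail, but both statements cannot stand as the primary outcome.

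**Working it through.** **1. The plan's own figure.** Inputs from the Sample size section: means 25.7 and 23.7 (difference 2.0), SDs 2.4 and 1.7, two-sided alpha 0.05, power 0.90, dropout 20%.

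- Printed formula: (1.96 + 1.28)² × (2.4² + 1.7²) / 2.0² = 10.498 × 8.65 / 4 = 22.7, so 23.
- Unequal-variance (Welch) t-test by noncentral t: power 0.889 at 23 per group and 0.902 at 24, so 24.
- Dropout: 24 / 0.8 = 30 per group, 60 in total.

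The stated 24 and 30 reproduce for one comparison at one time.

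**2. How each reading treats a split result.**

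| Reading | Week 2 significant only | Week 14 significant only |
|---|---|---|
| Sample size section (Week 2) | positive | negative |
| Two times, either suffices | positive | positive |
| Two times, both required | negative | negative |
| One repeated-measures ANOVA | depends on the effect tested (group, or group by time), not named | same |

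**3. Either time suffices, each at uncorrected two-sided 0.05.** Familywise error is P(|Z1| > 1.96 or |Z2| > 1.96) under a bivariate normal. The correlation between the two statistics is not in the document, so a range is shown.

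| Assumed correlation | Familywise error |
|---|---|
| 0 | 1 − 0.95² = 9.75% |
| 0.5 | 9.1% |
| 0.7 | 8.3% |
| 0.8 | 7.8% |
| 0.9 | 7.0% |

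Counting only false claims in favour of dual-target stimulation, the error runs from 4.9% (correlation 0) to 3.5% (correlation 0.9), against a nominal 2.5%.

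**4. Both times required.** There is no inflation. Assume the Week-2 difference and SDs also hold at Week 14. With 24 per group the standardised effect is 2.0 / √(8.65/24) = 3.33.

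- Normal approximation: power for both is 83.7% at correlation 0 and 88.7% at 0.9. On the same scale the single test has Φ(3.33 − 1.96) = 91.5%.
- Welch scale at correlation 0: 0.902² = 81.4%. The normal-approximation range is therefore optimistic by about two points.

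**5. Bonferroni across the two times (0.025 each), same assumed Week-14 effect.** Welch power per test at 24 per group is 83.8%. Reaching 90% needs 29 evaluable per group, and 29 / 0.8 = 36.25, so 37 enrolled per group (74 in total).

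**6. One time, Week 2, at 0.05.** The sample size is unchanged: 24 evaluable and 30 enrolled per group.

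**The case against.** A reader might infer that the plan gives two chances to succeed at 0.05 with no multiplicity rule, so that the type I error certainly exceeds 5%. The document does not support that.

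- It states no rule that either time suffices. If both are required, there is no inflation.
- It does contain a Bonferroni step. One might dismiss that step because two groups leave no further pairs to compare. But the wording on secondary outcomes implies a repeated-measures model for MoCA as well, and there the step could cover the group contrasts at Week 2 and Week 14.

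The words score and change might also be taken as incompatible. Under randomisation both have the same expected group difference and only their variances differ, so the real conflict is over the time points.

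Finally, the Trial design section calls the study exploratory, and testing order is often left to an analysis plan. The exploratory label lowers the weight of the familywise figures. It does not remove the contradiction, because the same document states a superiority hypothesis, a 90% power calculation and a binary significance rule.

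What remains after these points is that the two definitions differ, the deciding comparison is not named, and the Bonferroni step is incomplete: its comparisons are unspecified and the non-parametric branch has none.

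**Conclusion.** The point holds as an inconsistency in the printed text. The trial is sized on MoCA at Week 2, the analysis section makes MoCA change at Week 2 and Week 14 primary, and nothing resolves which decides success.

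The size depends on how the gap is filled. Familywise error of 7.0% to 9.75% applies only if either time counts without correction. Power of about 84% to 89% (normal approximation) applies only if both are required. The first range rests on assumed correlations from 0.9 to 0. The second also assumes that the Week-2 effect and SDs persist to Week 14. The stated sample size is right for the Week-2 endpoint, so it is not itself in error. The contradiction should be corrected before any outcome data are seen.

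**What to change.** - In Primary outcomes, Sample size and Statistical methods, state the same single primary endpoint: the between-group difference in MoCA at the Week-2 post-intervention assessment, tested at two-sided 0.05. Adjusting for baseline MoCA is preferable, since it is already collected, but the contradiction can be resolved without it.
- Name the model effect or contrast that is the primary test.
- Make Week-14 MoCA a key secondary endpoint, tested at 0.05 only if Week 2 is significant. This fixed order costs no alpha.
- Keep the Bonferroni sentence, but say which contrasts it covers and what applies in the non-parametric branch.

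The cost is wording only, and 24 evaluable and 30 enrolled per group stay valid. The downside is that Week 14 loses its primary label, and an effect seen only at Week 14 could not be claimed as confirmatory. If the sponsor wants both times as primary, the success rule must be stated and the trial re-sized with Week-14 inputs. With Bonferroni and the same assumed effect, that means 37 enrolled per group instead of 30.

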#### Implementation

The allocation sequence will be generated by an independent biostatistician who is not involved in participant enrollment, intervention delivery, or outcome assessment. A computer-generated randomization program will be used, stratifying participants by age and baseline cognitive function to ensure balance between groups.

Participants will be enrolled by study clinicians who are responsible for screening and performing baseline assessments. The clinicians involved in enrollment will not have access to the allocation sequence or any information about group assignments.

After a participant has been enrolled and completed their baseline assessments, the study clinician will contact a research assistant to retrieve the next sequentially numbered, opaque, sealed envelope. The envelope will be opened in the participant’s presence, and the group assignment will be revealed. The research assistant, blinded to the allocation sequence, will assign the participant to the corresponding intervention group.

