#### Methods in analysis to handle protocol non-adherence and any statistical methods to handle missing data

The primary analysis will follow an intention-to-treat (ITT) approach, including all participants as randomized, regardless of protocol adherence.

Missing data will be addressed using multiple imputation methods, assuming data are missing at random. Imputation models will include baseline characteristics, group assignment, and observed outcome values.

Sensitivity analyses will be conducted to assess the robustness of the results under different missing data assumptions, including complete case analysis and worst-case scenario imputation.

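### The primary MoCA test is an unadjusted ANOVA on change, switched to a rank test if the data look non-normal; one baseline-adjusted model would be more precise and would fix the effect measure in advance

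*Protocol article*

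**What the plan says.** All places are in the protocol article.

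- **Endpoint and test** (Statistical methods for primary and secondary outcomes). The endpoint is a change: "The primary outcome of this study is the change in MoCA scores from baseline to post-intervention and follow-up". The test depends on the look of the data: "For normally distributed continuous data, ANOVA will be used to compare differences between the two groups", and otherwise "For non-normally distributed continuous data, the Wilcoxon test will be used". No covariate is named for this test. The only covariates mentioned for any outcome are optional: "Exploratory analyses may include lesion location and laterality as covariates if appropriate, to explore their influence on intervention outcomes".
- **Randomisation** (Implementation). The sequence is generated by "stratifying participants by age and baseline cognitive function to ensure balance between groups".
- **Missing data** (Methods in analysis to handle protocol non-adherence and missing data). "Missing data will be addressed using multiple imputation methods, assuming data are missing at random". Baseline characteristics go into the imputation model; nothing puts them into the analysis model.
- **Sizing** (Sample size). "The primary outcome measure for this trial is the MoCA score after 10 treatment sessions", with post-treatment means "assumed to be 25.7 and 23.7, with standard deviations of 2.4 and 1.7, respectively".

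The secondary outcomes are to be analysed by repeated-measures ANOVA described as similar. If the primary test is read that way too, its baseline-to-post group-by-time test is the same as the change-score test and is still unadjusted.

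**The concern.** The design treats age and baseline cognition as important enough to stratify on, and the stated analysis then leaves both out. Two things are at stake.

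1. **Precision.** Subtracting baseline forces a slope of 1 on it. The best slope is the baseline-to-post correlation times the ratio of SDs, which is below 1 when the SDs are similar. The change score therefore over-corrects and carries extra noise. Leaving the stratification out also makes the reported standard error too large, so the balance gained by stratifying is not turned into power.
2. **A defined effect measure.** The ANOVA compares mean changes and the rank test compares distributions. If a normality check on the trial's own data decides between them, the reported effect, and the quantity to be pooled over imputed datasets, is not known until the data are seen.

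**Working it through.** **Inputs from the document.** Means 25.7 and 23.7 (difference 2.0); SDs 2.4 and 1.7; two-sided 5%; 90% power; 24 per group, or 30 after 20% dropout.

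**Assumptions.** The baseline-to-post correlation r is not given, so a range is shown. A common SD at both visits is assumed: √[(2.4² + 1.7²)/2] = √4.325 = 2.08.

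**The plan's own figure.** The printed formula gives (1.96 + 1.28)² × (5.76 + 2.89) / 2² = 10.50 × 8.65 / 4 = 22.7, so 23. The unequal-variance t-test that the protocol names has power 0.889 at 23 and 0.902 at 24, so 24 is right. 24 / 0.8 = 30. The sizing reproduces, but it is for the post-treatment score, not for change.

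**Variance per patient.** Post score: s². Change: 2s²(1 − r). ANCOVA: s²(1 − r²). The ratio of ANCOVA to change is (1 + r)/2, below 1 for every r below 1.

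**Power at 24 per group, difference 2.0** (noncentral t, SE = √(2 × variance / 24)):

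| r | ANCOVA / change variance | SE change | SE ANCOVA | Power change | Power ANCOVA |
|---|---|---|---|---|---|
| 0.3 | 0.65 | 0.71 | 0.57 | 79% | 93% |
| 0.5 | 0.75 | 0.60 | 0.52 | 90% | 96% |
| 0.6 | 0.80 | 0.54 | 0.48 | 95% | 98% |
| 0.7 | 0.85 | 0.47 | 0.43 | 98.8% | 99.5% |
| 0.9 | 0.95 | 0.27 | 0.26 | near 100% | near 100% |
| 0.96 | 0.98 | 0.17 | 0.17 | near 100% | near 100% |

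At r = 0.5 the change score has the same variance as the post score. Below that it is less precise than the comparison on which the trial was sized, and the planned 90% is not reached.

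**Baseline imbalance.** Given a realised imbalance, the change-score difference shifts by (r − 1) times that imbalance. Under simple randomisation with 30 per group, one standard error of the imbalance is 2.08 × √(2/30) = 0.54 point. The shift is 0.5 × 0.54 = 0.27 point at r = 0.5 and 0.3 × 0.54 = 0.16 point at r = 0.7. Stratifying on baseline cognition makes it smaller.

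**Simulation** (24 per group, 4,000 trials per setting, SD 2.08, stratified at the median of baseline; age not modelled):

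- r = 0.5: the unadjusted change test reports a mean SE of 0.60 against a true SE of about 0.55. Its type I error is 3.2%, against 4.8% for ANCOVA. Power for a 1.2-point effect is 49% against 60%.
- r = 0.7: type I error is 4.8% against 5.4%, and power is 73% against 78%.
- For a true effect of 1.2 the unadjusted estimate averaged 1.19 to 1.20 over all settings with normal data.
- A normality pre-test sent 9% to 10% of truly normal trials, and about 66% of trials with skewed errors, to the rank test. Type I error of the two-stage procedure was 5.4% to 5.5% without stratification, close to that of the plain change test, and 2.7% to 4.8% with it. The switch did not inflate it.

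**The case against.** **Baseline is not ignored.** Correct: the change score subtracts it. The complaint is only that it is not regression-adjusted.

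**There is no bias.** Correct on average. A reader might infer that the unadjusted comparison is biased by chance imbalance. Over randomisations it is unbiased; the shift exists only conditional on the imbalance that occurs, and the planned stratification limits that.

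**The gain may be negligible.** This stands as a caution. The only correlation the protocol gives is a MoCA test-retest reliability of 0.96, at which the variance gain is 2%. That figure is not the baseline-to-post correlation in treated patients. The entry limit of MoCA below 26 and the mix of subacute and chronic stroke may lower the correlation in this sample, but the document does not say by how much. A large loss of power needs a correlation of about 0.5 or below.

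**The normality switch and the missing strata do no harm to error rates.** Correct. A reader might infer a raised false-positive rate; the simulation shows none, and ignoring the stratification makes the test conservative. What remains is lost power and an effect measure chosen by the data.

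**The secondary analyses.** A reader might also infer that repeated-measures ANOVA would dilute the effect by averaging in the baseline visit. The text says that changes are analysed, which exist at two visits after baseline, so this does not follow.

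**The trial is called exploratory, and details belong in an analysis plan.** Neither removes the point. The trial is sized at 90% power with a two-sided 5% test, and the ANOVA-or-Wilcoxon rule is fixed in the protocol text itself.

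**Conclusion.** The point holds as one of efficiency and clear prespecification. The stated primary test is less precise than ANCOVA for every correlation below 1, and conservative to the extent that stratification on baseline cognition is left out. The cost in power, under a common SD of 2.08 and 24 per group, runs from 14 percentage points at r = 0.3 through 6 at r = 0.5 to under 1 at r = 0.7. These figures rest on the protocol's own SDs and on an assumed correlation. If the true SDs are larger or the true effect smaller than planned, the gap at a given correlation can be wider, as the 1.2-point simulation shows. The documents do not support a claim of inflated type I error or of average bias. The change should be made, but its absence would not invalidate the trial.

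**What to change.** In the statistical methods section, replace the ANOVA-or-Wilcoxon rule with one prespecified linear model (ANCOVA):

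- Outcome: post-intervention MoCA, the endpoint on which the trial was sized. Terms: group, baseline MoCA and age.
- Report the adjusted mean difference with its 95% confidence interval, using robust standard errors because the planning SDs differ between groups.
- Fit the model in each imputed dataset and pool by Rubin's rules.
- For the follow-up visit use the same model, or fit one mixed model over both visits. The statistical section names both visits in the primary outcome while the sample size rests on the first, so the choice of primary time point must be stated openly and not left implied by the model.
- Drop the normality gate and keep a rank test as a sensitivity analysis only.
- Use the same model for DST, TMT-A, TMT-B and MBI, each with its own baseline.

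The cost is a wording change in the protocol, carried into any analysis plan before unblinding. Baseline scores are already collected and age is already a stratification factor, so no patients, visits or measurements are added.

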The dorsolateral prefrontal cortex (DLPFC) and angular gyrus (AG) are two critical brain regions implicated in cognitive processes. DLPFC is an important target for brain stimulation because it plays a key role in cognitive functions like memory, attention, and decision-making. It is part of the central executive network, which helps manage and coordinate complex mental tasks. Stimulating the DLPFC can increase brain activity, improve connections with other brain areas like the caudate nucleus, and support recovery of thinking abilities, making it a valuable focus for treating cognitive problems after a stroke (Han et al., 2023). The AG located in the posterior part of the inferior parietal lobule at the junction of the parietal, temporal, and occipital lobes, acts as a crucial convergence zone for multisensory and conceptual integration. It is an important hub in several neural networks, including the Default Mode Network for memory retrieval and self-referential processing, the Central Executive Network for working memory and attention control, and the Cross-Modal Integration Network for sensory-conceptual integration (Seghier, 2013). Functionally, the AG supports higher-order cognitive tasks including semantic processing, episodic memory retrieval, attentional regulation, numerical reasoning, spatial cognition, and social understanding, bridging perception with advanced cognitive processes (Seghier, 2023). In Alzheimer’s disease and mild cognitive impairment (Yang et al., 2022), stimulation of the AG has been shown to improve cognitive functions.

This trial aims to evaluate the clinical efficacy of dual-target a-tDCS targeting the DLPFC and AG in patients with PSCI and to investigate the underlying neural mechanisms using fNIRS. We hypothesize that dual-target a-tDCS will outperform single-target a-tDCS in improving cognitive function and enhancing brain connectivity.

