#### Secondary objectives

The secondary objectives are to investigate the neural mechanisms underlying the effects of these tDCS interventions using fNIRS. Specifically, we aim to:

(1) Assess changes in brain activation in the DLPFC and AG regions.(2) Evaluate the impact of dual-target a-tDCS on functional connectivity between cognitive networks associated with PSCI.(3) Explore the correlation between changes in brain activity and cognitive improvements observed in PSCI patients.

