#### Methods for additional analyses (e.g., subgroup analyses)

Subgroup analyses are not planned for this study.

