## Discussion

The DLPFC is pivotal in multiple cognitive processes, such as working memory, planning, inhibition, and abstract reasoning. Previous studies indicate that stimulation over the DLPFC can effectively improve cognitive deficits in stroke patients (Shaker et al., 2018; Cha et al., 2022). The AG also plays a vital role in various cognitive functions, including attention, spatial cognition, mental arithmetic, visuospatial processing, inhibitory control, theory of mind, and the processing of semantic information (Bonner et al., 2013; Grob et al., 2024; Park et al., 2024). Stimulation of the AG could enhance autobiographical memory integration (Bonner et al., 2013) and improve associative memory performance (Wang et al., 2014).

Building on these findings, this study hypothesizes that dual-target a-tDCS, focusing on both the DLPFC and AG, will be more effective in improving cognitive function in patients with PSCI compared to single-target a-tDCS on DLPFC. We anticipate significant enhancements in overall cognitive performance, specifically in domains like memory and executive function. Furthermore, we expect that fNIRS measurements will reveal increased activation in the DLPFC and AG and enhanced functional connectivity between cognitive brain networks.

If these hypotheses are confirmed, dual-target a-tDCS could become an effective intervention to improve cognitive outcomes in PSCI patients, potentially exceeding the benefits of conventional single-target interventions. This approach may be integrated into existing rehabilitation programs, thereby contributing to better recovery and an improved quality of life for stroke survivors.

However, the study has several limitations. The sample size is relatively small, and it is a single-center study, which may affect the generalizability of the results. The lack of long-term follow-up means that we could not assess the long-term effects of the intervention. Future research should aim to overcome these limitations by conducting multi-center trials with larger cohorts and longer follow-up periods.

Further exploration is necessary to assess its efficacy across different types and severities of PSCI.

The absence of a dual sham stimulation group may limit the interpretation of tDCS-specific effects versus non-specific intervention effects. Future studies may consider including a dual sham group to further strengthen causal inferences.

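### The brain–cognition correlation for secondary objective 3 has no term for arm, so a pooled coefficient would partly restate the treatment effect if both outcomes differ by arm

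*Protocol article*

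**What the plan says.** Under Secondary objectives, the third aim of the protocol article is to "Explore the correlation between changes in brain activity and cognitive improvements observed in PSCI patients". The only method that matches it is one sentence under Statistical methods for primary and secondary outcomes: "Correlation analysis, such as Pearson correlation coefficient or Spearman correlation coefficient" "will be conducted to explore the relationships between primary and secondary outcome measures".

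Three nearby statements bear on how that sentence is read:

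- The sentence before it puts arm into the fNIRS mixed model, "accounting for random effects of participants and fixed effects of group and time". Arm is not mentioned for the correlation.
- The covariates named in that section are other variables: "Exploratory analyses may include lesion location and laterality as covariates if appropriate".
- Under Methods for additional analyses: "Subgroup analyses are not planned for this study".

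The hypothesis closing Background and rationale is comparative for both kinds of outcome: "We hypothesize that dual-target a-tDCS will outperform single-target a-tDCS in improving cognitive function and enhancing brain connectivity". The Discussion adds that "we expect that fNIRS measurements will reveal increased activation in the DLPFC and AG", without saying whether this is a contrast between arms.

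**The concern.** Two variables whose means both differ between arms are correlated in the combined sample even if they are unrelated among patients within each arm. The between-arm separation alone tilts the scatter. Objective 3 asks a patient-level question: do patients whose brain measure changes more also improve more in cognition? A pooled Pearson or Spearman coefficient mixes that question with the treatment effect, and it does so exactly when the trial's own hypotheses are true. A positive coefficient could then be read as support for a mechanism when it only shows that both outcomes moved with allocation.

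**Working it through.** **The plan's own figure first.** The inputs from Sample size are means of 25.7 and 23.7 (difference 2.0), SDs of 2.4 and 1.7, two-sided α = 0.05 and power 0.90.

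- Printed formula: (1.96 + 1.28)² × (2.4² + 1.7²) / 2.0² = 10.4976 × 8.65 / 4 = 22.7, so 23 per group.
- Unequal-variance t-test (noncentral t): power is 0.889 at 23 and 0.902 at 24, so 24 per group, as stated.
- Dropout of 20%: 24 / 0.8 = 30 per group, 60 in total, as stated.

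These figures reproduce. The article gives no figure for the correlation.

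**Standardised MoCA effect.** The average SD is √((2.4² + 1.7²)/2) = √4.325 = 2.08, so d1 = 2.0 / 2.08 = 0.96. The planning values are post-treatment scores; they are assumed here to apply to change.

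**fNIRS arm effect.** The article gives none. An assumed range of d2 = 0 to 0.96 SD is used.

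**Pooled correlation with zero within-arm correlation, 1:1 allocation:**

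ρ = (d1·d2/4) / √((1 + d1²/4)(1 + d2²/4))

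With d1 = 0.9617, d1²/4 = 0.231. Two examples:

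- d2 = 0.3: 0.0721 / √(1.231 × 1.0225) = 0.0721 / 1.122 = 0.064
- d2 = 0.96: 0.231 / 1.231 = 0.188

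**Rejection rates.** These come from a simulation of the Pearson coefficient with 20,000 replicates per row. Outcomes are independent normal within arm with equal variances, tested two-sided at 5%. N = 48 is the planned evaluable number and N = 60 the number enrolled.

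| d1 | d2 (assumed) | ρ | P<0.05, N = 48 | P<0.05, N = 60 |
|---|---|---|---|---|
| 0.96 | 0 | 0.00 | 5.0% | 5.2% |
| 0.96 | 0.3 | 0.06 | 7.1% | 7.5% |
| 0.96 | 0.5 | 0.10 | 10.9% | 12.4% |
| 0.96 | 0.8 | 0.16 | 20.2% | 23.3% |
| 0.96 | 0.96 | 0.19 | 25.5% | 30.4% |
| 0.5 | 0.3 | 0.04 | 5.6% | 5.8% |
| 0.5 | 0.96 | 0.11 | 10.9% | 12.4% |

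The last two rows show a MoCA effect about half the planned size.

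**Conditioning on arm.** When each outcome is centred on its arm mean (the partial correlation given group), the mean coefficient is about 0.00 and the rejection rate is 4.7–5.2% in every scenario run.

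Spearman was not simulated. The same mechanism applies to it, since ranks also separate by arm.

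**The case against.** **Pooling is inferred.** No sentence says whether the coefficient is pooled, per arm or partial. The wording offers the two coefficients as examples, and an analysis plan that is not shown could condition on arm. This stands as a limit on certainty. It does not remove the point: the article names a method rather than leaving it open, names arm in the sentence before but not here, and plans no subgroups. Pooling is therefore what someone following the text would do.

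**A pooled coefficient may be a legitimate description.** Its population value really is non-zero when both arm effects exist, and exceeding 5% is an error only against a within-arm null that the article does not state. As description, that is fair. But the correlation sits under objectives about neural mechanisms, and for patient-level association the pooled value is the wrong quantity.

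**The arm effect on fNIRS may be small.** The explicit comparative hypothesis concerns connectivity. The Discussion's expectation about activation is not worded as an arm contrast, and both arms receive active DLPFC stimulation. This stands, and it is why the assumed range goes down to zero.

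**Stronger readings that a reader might infer, and that the article does not support:**

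- *That the plan fails to say changes are correlated.* Objective 3 speaks of changes, and the statistical section defines the primary outcome and the DST, TMT and MBI outcomes as changes.
- *That this is the trial's only mechanistic analysis.* The fNIRS mixed models, with group and time, serve the first two aims, on activation and connectivity. The correlation serves only the third.
- *That a false brain–cognition link would usually appear.* Even in the most extreme scenario, about 7 trials in 10 would show no significant correlation.

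**Conclusion.** The point holds as a matter of analysis choice. Read naturally, the method named for objective 3 does not separate patient-level association from the treatment effect, and its coefficient is biased away from zero when cognition and the fNIRS measure both differ by arm.

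With the planned MoCA effect and assumed fNIRS effects of 0.3 to 0.96 SD, the bias is modest in size (about 0.06 to 0.19). It is not negligible in error rate: about 7–26% at N = 48 and 7.5–30% at N = 60, instead of 5%. If the MoCA effect is 0.5 SD, the range is about 6–12%. If fNIRS does not differ by arm, there is no inflation.

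This rests on four assumptions: the coefficient is pooled, the within-arm correlation is zero, the post-treatment planning values carry over to change, and the fNIRS effects, which the article does not give, lie in the assumed range. The trial and this analysis are exploratory, and the primary between-group comparison on MoCA is not touched.

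**What to change.** Add a sentence to the statistical section. For objective 3, the change in the cognitive score is related to the change in the fNIRS measure by a partial correlation (Pearson or rank) adjusted for group, or by a regression of cognitive change on fNIRS change with group as covariate. Report the two within-arm coefficients alongside, and state that an unadjusted pooled coefficient, if shown at all, is descriptive and not evidence of mechanism.

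The cost is one degree of freedom. No new data, visits or patients are needed. The within-arm coefficients will be imprecise at 24 to 30 patients each, so they should be given with confidence intervals.
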